**PROTOCOL VERSIONS**

| **Versions No** | **Version Date** | **Protocol updated & finalised by;** | **Appendix No detail the reason(s) for the protocol update** |
| --- | --- | --- | --- |
| 1.1 | 17^th^ July 2019 | **Updated by**: [name]  **Finalised by:** [name] | Updated in line with REC feedback |
| 2.0 | 5^th^ August 2019 | **Updated by**: [name]  **Finalised by:** [name] | Updated in line with REC feedback |
| 2.1 | 12^th^ Nov 2019 | **Updated by**: [name]  **Finalised by:** [name] | The protocol has been amended to allow men to participate if they have a PSA value 20 ng/ml or less with the value recorded <12 months before study entry. |
|  |  |  |  |

**STUDY SUMMARY**

| **Identifiers** | | |
| --- | --- | --- |
| IRAS Number | 251166 | |
| REC Reference No | 19\LO\1128 | |
| Sponsor Reference No | 123973 | |
| Other research reference number(s) (if applicable) | CPMS: 42576 | |
| Full (Scientific) title | A prospective cohort study in men with a suspicion of prostate cancer who are referred onto an MRI-based diagnostic pathway with donation of tissue, blood and urine for biomarker analyses | |
| Health condition(s) or problem(s) studied | Prostate cancer | |
| Study Type | Single arm multi-site prospective longitudinal cohort study with blood, urine and tissue donation | |
| Target sample size | Men with PIRADS/LIKERT MRI lesions of score 3, 4 or 5 undergoing a targeted and systematic biopsy | |
| **STUDY TIMELINES** | | |
| Study Duration/length | **First patient recruited:** 1^st^ September 2019  **Last patient recruited:** 31^st^ May 2021  **Follow-up:** Indirect data collection via healthcare data linkage 31^st^ May 2024 | |
| Expected Start Date | 1^st^ September 2019 | |
| End of Study definition and **anticipated date** | **Cross Sectional component**   - **LPLV:** 31^st^ May 2021 - **Database Lock:** 31^st^ May 2022   **Longitudinal component**   - **3 years after LPLV:** 31^st^ May 2024 | |
| **FUNDING & Other** | | |
| Funding | Medical Research Council (MRC) and Cancer Research UK (CRUK) | |
| Other support | Commercial organisations that sign up to the consortium agreement to become ReIMAGINE partners will be providing *in-kind* contributions. | |
| **STORAGE of SAMPLES** | | |
| Human tissue samples | **Biological samples will be transferred to and processed at:**  The laboratories of [name], at UCL Cancer Institute, [name]  Aliquots will be sent to partners as per the ReIMAGINE Consortium agreement. | |
| Data collected / Storage | All identifiable data will be held on secure servers hosted and maintained by University College London (UCL).  Pseudonymised data, including imaging and histology data, will be held by UCL and transferred to central secure servers held in the EU and managed by Philips.  Pseudonymised MRI DICOM images and related annotations will be uploaded to the CRUK funded National Cancer Imaging Translational Accelerator (NCITA) image repository before a copy is shared with Philips via the XNAT platform. | |
| **KEY STUDY CONTACTS** |  | |

**KEY ROLES AND RESPONSIBILITIES**

**SPONSOR:** The sponsor is responsible for ensuring that, prior to commencement of a study, the necessary arrangements are in place for the research team to access resources and support the delivery of the research as proposed. The Sponsor is equally responsible for allocating responsibilities for the management, monitoring and reporting of the research. Additionally, the Sponsor must be satisfied that there is agreement on appropriate arrangements to record, report and review significant developments as the research proceeds, and approve any modifications to the study design.

**FUNDER:** The funder is the entity that will provide the funds (financial support) for the conduction of the study. Funders are expected to provide assistance to any enquiry, audit or investigation related to the funded work.

**CHIEF INVESTIGATOR (CI):** The person who takes overall responsibility for the design, conduct and reporting of a study. If the study involves researchers at more than one site, the CI takes on the primary responsibility whether or not he/she is an investigator at any particular site.

The role of the CI is to complete and to ensure that all relevant regulatory approvals are in place before the study begins. They are also responsible for ensuring arrangements are in place for good study conduct, robust monitoring and reporting, including prompt reporting of incidents. Such processes include the provision of adequate training for study staff to conduct the study as per the protocol and relevant standards.

The Chief Investigator is responsible for the submission of annual reports as required. The Chief Investigator will notify the Research Ethics Committee (REC) of the end of the study, including any reasons for the premature termination. Within one year after the end of study, the Chief Investigator will submit a final report with the results, including details of any publications/abstracts, to the REC.

**PRINCIPLE INVESTIGATOR (PI):** Individually or as leader of the researchers at a site; ensuring that the study is conducted as per the approved study protocol, and reporting/notifying the relevant parties – this includes the CI of any breaches or incidents related to the study.

# INTRODUCTION

Prostate cancer diagnosis has undergone considerable change over the last decade with an increasing uptake of multi-parametric MRI (mpMRI) prior to prostate biopsy. In the past, most men underwent a transrectal ultrasound guided (TRUS) biopsy without knowledge of whether a man had cancer or not, and if there was a cancer, blind to its location. Currently, UK practice is approaching a point where mpMRI is likely to become part of the standard-of-care with the UK’s National Institute for Health and Care Excellence (NICE) issuing guidance recommending that an mpMRI be offered to all men prior to a prostate biopsy ([www.nice.org.uk/guidance/indevelopment/gid-ng10057](http://www.nice.org.uk/guidance/indevelopment/gid-ng10057)).

This modification to the prostate cancer diagnostic pathway has resulted in significant consequences to men at risk. These are likely to comprise the following based on the evidence accumulated in high quality prospective studies: fewer men biopsied overall; fewer needle deployments; less over-diagnosis; fewer missed clinically important cancers; and less overall harm to the patients ([name] H *et al.* Lancet 2017; Kasivisvanathan V *et al.* NEJM 2018). These benefits arise from the ability of mpMRI to locate clinically significant prostate cancer as mpMRI positivity is positively associated with both tumour grade and volume – the two prostate cancer attributes most associated with risk.

The result is a process of risk stratification that is about 100% better ([name] H *et al.* Lancet 2017). than that which preceded the mpMRI based approach and results in a concordance with verified pathology on whole-gland step section (following surgical removal) of around 90% (Baco E *et al.* Eur Urol 2015).

This new level of precision creates problems as all the risk models currently in use for prostate cancer risk estimation are based on data derived from a TRUS biopsy pathway. Because the methods prior to mpMRI used a combination of PSA and transrectal ultrasound (TRUS) guided biopsy men, invariably, had their risk under-estimated in a number of ways. First, they were told they were clear when they were not. Second, few men with anterior disease were ever diagnosed. Third, the Gleason grade was under-estimated in 30-50% of cases. The result of these risk-stratification errors – perhaps the greatest in all of the cancer field – was that men had either no treatment (when they needed it), or delayed treatment (when it should have been given quicker) or inappropriate treatment (when it was not needed at all due to an unimportant indolent cancer diagnosis).

The other consequence relates to our understanding of prostate cancer – and is much less well appreciated. This is the fact that the spectrum of cancer that we have been diagnosing for the last 50 years is a function of the performance of the tests we have used historically and is therefore considerably skewed against the true spectrum of disease that exists.

There exist known and unknown errors that will result from applying old risk-stratification methods to the new outputs of an image-based diagnostic pathway. The main error that results is that risk will be over-estimated (when cancer is present) for most of the men that are diagnosed if we superimpose the histological profile of tissue acquired as a result of an MRI-targeted biopsy as opposed to a TRUS guided biopsy in the same man. Typically, the TRUS-biopsy derived tissue will have fewer cores that are positive, reduced maximum cancer core lengths and a lower overall Gleason attribution.

As there is no obvious method to adjust for this error the general view is that new and better risk-stratification and prediction models will need to be created using inputs that are derived from men undergoing a contemporary assessment. It was to address this particular challenge that the ReIMAGINE Consortium was conceived of and created.

**ReIMAGINE Prostate Cancer Risk** constitutes the principal component of ReIMAGINE and was designed to risk-stratify men as accurately as is currently possible within a contemporary MR-imaging-based diagnostic pathway. It was designed to create an opportunity for the many commercial entities that exist that have developed biomarkers to assist in making the risk stratification of these men more precise. Most, if not all, of these biomarkers were developed to correct the errors associated with TRUS guided biopsy. They now would benefit from being re-calibrated to the new image-based pathway. ReIMAGINE will create a platform designed to assist in this task – both at cross sectional risk-stratification (precise diagnosis) but also down-stream prediction of key events such as clinical progression, time to metastases and death. Further, ReIMAGINE will permit the discovery and validation of novel clinical, fluidic, histological and imaging biomarkers, alone or in combination, by the biobanking and data banking of patient derived samples.

**Figure 1: ReIMAGINE Prostate Cancer Risk patient flow**

[figure not shown]

# BACKGROUND AND RATIONALE

For the last 50 years PSA-biopsy risk-stratification has been applied to men at risk of prostate cancer, which is now known to be unfit for purpose. PSA-biopsy risk-stratification results in the greatest burden in all oncology of over-diagnosis, over-treatment, and of missed cancers that are of clinical importance. This systematic error has biased tissue archives, skewed risk calculators, and rendered studies un-representative and undermined policy-making. MRI has been shown to provide almost complete correction for each error associated with the traditional PSA-biopsy approach by identifying a distinct stratum from the wider population at risk that is closely correlated to the two strongest progression predictors - grade and volume. Encouraged by the patient/user groups within the ReIMAGINE consortium, the aim has been to create a novel, image based, measurable-disease endotype and to use it to risk stratify men with prostate cancer and, as a result, improve the ability to derive prognostic information and allocate men to the most appropriate and effective therapies. This will be achieved by creating unique cohorts, each defined by the presence of a specific MRI-derived endotype that will provide clinical, molecular and radiological inputs into a progression model that will be specified to predict disease status, radiological, clinical and metastatic progression. During this process, insight into the key mechanistic events that drive progression will be available for the first time. Machine learning algorithms from the radiology-pathology annotated training data sets will inform computer-assisted diagnosis. There will be a number of commercial partners (that have created biomarkers to risk-stratify, predict and prognosticate) who will generate further their work as a result of the opportunity that ReIMAGINE provides to refine their performance by means of enhanced precision and, in addition, create new risk models that integrate MRI-derived radiomics with their improved proprietary offerings.

ReIMAGINE Prostate Cancer Risk seeks to exploit a novel and improved diagnostic pathway for men at risk of prostate cancer. This pathway is in its most advanced state of implementation in London (UK), largely as a result of its early implementation and on the successful delivery of the PROMIS study - level-1 evidence showing the superiority of MRI over traditional diagnostic measures. For this reason the ReIMAGINE consortium has chosen to base this study in hospital groups where prostate MRI is in an advanced state and offered as standard of care within an NHS setting. Participants will comprise NHS patients who have undergone a high-quality prostate MRI as part of routine NHS care in preparation for a decision on whether or not to proceed to biopsy. In partner hospitals - but not necessarily standard elsewhere - men with abnormalities in their prostates conforming to Likert/PIRADS 3-5 are offered targeted biopsies. It is at this point that men would be approached and informed about the study and their consent sought. As some sites run prostate cancer “one-stop” clinics the protocol will allow the option of explaining and discussing consent over the telephone. The study therefore is not changing the standard of care - merely exploiting it to explore the opportunity to follow these men a little more closely and seek permission to obtain tissue (from the biopsy), blood and urine so that synergies between the imaging phenotype and the manifestation of molecular changes that appear in the tissue and fluid samples can be explored. Once this process is complete, men return to standard of care, but their consent is sought for healthcare data linkage. ReIMAGINE Prostate Cancer Risk is seeking to deeply phenotype 1,688 men in this way in the least disruptive and most cost-efficient way possible.

One other huge opportunity is to use the ReIMAGINE platform to define what it is we mean by the term ‘clinically important’ or ‘clinically significant’ prostate cancer. There is no agreed threshold that makes the literature difficult, if not impossible, to interpret as each study group is seeking to predict a different disease entity. The current consensus is that the presence of any Gleason pattern 4 constitutes clinical significance. This was the definition we used in PRECISION (Kasivisvanathan V *et al.* NEJM 2018). This is almost certainly too low a threshold given the recent publication of the 29-year follow-up of the SPCG-4 study (Bill-Axelson A *et al.* NEJM 2018). This showed that death from prostate cancer was not associated with Gleason 3 plus 4 disease. Risk came from higher grade (Gleason 4 plus 3 or more) and/or extra-capsular extension. In PROMIS any Gleason 4+3 or greater or a cancer core length of greater than 5mm of any grade was used. This is a disease endo-type that is invariably captured by mpMRI ([name] et al, Lancet, 2018). Because we are following the ReIMAGINE cohort to ultimate death (with appropriately secured funding) we should be in a good position to define the baseline characteristics that are associated with both a prostate cancer-related death and the important clinical events that tend to precede it.

ReIMAGINE Prostate Cancer Risk will create the first set of cohorts of men with localized prostate cancer in which truly representative tissue will be procured. The result is an opportunity to phenotype prostate cancer in a manner that has not been possible to date. The discernible sub-groups that emerge should, as consequence, be free of the prognostic imprecision that has hampered our attempts at both risk assessment and appropriate treatment allocation.

We hypothesise that tumour molecular complexity and intra-tumour heterogeneity (ITH) integrated with imaging will improve risk stratification over and above the current best predictor– histological grade. Studies have shown that ITH positively associated with poor prognosis in prostate and lung cancer (Fraser N, Nature 2017; Jamal-Hanjani M, NEJM 2017). Ongoing efforts to extensively characterise the genome/exome, transcriptome and methylome of localized and advanced prostate cancer provide a resource of molecular data that we vertically integrate with the profiling of more advanced disease (STRATOSPHERE).

Our industry partners are developing algorithms to detect at high-resolution tumour DNA in plasma that will be evaluated for associations with risk of progression. By integrating with matched tumour multi-region sequencing data and complementing with high-coverage targeted NGS performed separately on the extracted plasma DNA, we aim to identify independent predictors of progression detected in circulation prior to biopsy and track sub-clonal relapse in follow-up samples.

This protocol has been informed, developed and approved in collaboration with patient and public involvement initiatives occurring in parallel with preparation of this submission. Additional experience is based on investigators’ experience in the PROMIS trial which successfully recruited on time and led to a change in pathway, has been incorporated into this protocol ([name] H *et al.* Lancet 2017). PRECISION, an international, multi-centre randomised study that compared an mpMRI based pathway with the standard of care (TRUS-Biopsy) showed that the MRI-based pathway was superior in terms of the proportion of men with clinically significant disease that were identified, the reduction in over-diagnosis that occurred and the observation that less harm was experienced by those randomised to mpMRI. Our previous PROGENY study also showed that the principle of imaging characterisation followed by diagnostic and research biopsy samples had a high uptake by patients with 80% of men approached agreeing to consent to the study [Linch et al, 2017/18, Annals of Oncology].

# OBJECTIVES

**Cross Sectional Component objective**

To develop a robust baseline risk stratification system for men who are referred with a suspicion of prostate cancer. By risk we mean the probability of harbouring clinically significant prostate cancer.

We aim to explore this risk in relation to characteristics measured in men at baseline. These characteristics will be collected from clinical records, mpMRI images, blood, urine and biopsy tissue samples.

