**Longitudinal Component objective**

To create and develop new and improved risk stratifications models for men diagnosed with prostate cancer. By risk we mean the probability of developing cancer, cancer progression, metastasis and death.

We aim to explore this risk in relation to characteristics measured in men at baseline. These characteristics will be collected from clinical records, mpMRI images, blood, urine and biopsy tissue samples.

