## Primary Outcome

### **Cross sectional component primary outcome**

Presence of clinically significant prostate cancer confirmed on biopsy, defined as any Gleason pattern 7 or greater.

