***Demographic and general measurements***

- Medical history
- Demographics
- Family History
- Ethnicity
- Age
- Co-Morbidities
- Medication use

All consented patients who are deemed eligible will have already been advised and/or have a scheduled visit for a prostate biopsy on clinical grounds as standard care. On the day of consent or at the time of the scheduled prostate biopsy participants will have the below interventions:

- Donation of blood will be drawn from men, either via a trained phlebotomist or from the cannula already in situ in preparation for their prostate biopsy.
- Donation of urine. Provided by participant in advance of prostate biopsy.
- Up to three additional biopsy cores will be taken at the time of the standard of care biopsy. Two cores will be taken from the radiologically guided area of suspicion and one control sample from the contralateral non-suspicious area.

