**Statistical Analysis**

All statistical analyses will be conducted according to pre-specified statistical analysis plans that will be agreed prior to the inspection of any outcome data. Logistic regression modelling will be used to analyse the factors associated with presence of clinically significant cancer. Cox regression modelling (or other appropriate survival methods if there is evidence of non-proportional hazards) will be used to analyse the factors associated with time to new cancers, progressions, metastases and deaths. Initially a list of pre-specified factors will be agreed and these will be analysed in the models using a stepwise approach to identify those that are independently associated with the outcome.

In addition to the simple frequentist analysis approach, a more sophisticated analysis will be conducted. We will first apply the SaddlePoint Signature multivariate Bayesian regression pipeline, which was designed specifically for regression with high-dimensional covariates, in order to generate (i) optimal predictive covariate selections (suppressing false positive associations), (ii) quantitative characteristics of true associations (including covariate interactions, if relevant), (iii) personalised multivariate risk signatures, and (iv) quantifiers of the degree of outcome predictability. This will be done both for the full covariate set and for the individual covariate streams (e.g. imaging, genomic, phenotypic), allowing us to compare the outcome prediction power of different information sources, and their potential synergy. The most recent version of the pipeline (version 2.8.6), uses advanced overfitting correction protocols (based on the replica method) and robust internal validation processes. The risk scores for the separate streams will provide intuitive visualisations of the heterogeneity of the patient cohort. In a second stage we will apply Bayesian multivariate latent class analysis, using the source-specific risk signatures computed in the first stage as meta-covariates, and assess whether and how the cohort should be further stratified into subgroups with distinct associations and/or base hazard rates.

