## Paraffin and H&E slide collection

In addition to the samples collected at visit 1, all sites will send H&E slides and FFPE tissue blocks to Professor [name]’s laboratory (facilitated by the ReIMAGINE clinical trial practitioners).

H & E slides will be anonymised, scanned using high resolution scanners and uploaded to the ReIMAGINE image warehouse. Scanned H&Es could be subjected to additional central pathology assessment and morphological features captured using computer-based algorithm to identify H&E based biomarkers for improved patient risk stratification. Scanned H&Es could also be shared with partners to integrate with analyses of scans and molecular biomarkers.

A tissue technician will also acquire slices from the requested FFPE tissue blocks in line with the study SOP. The acquired slices will be stored in the [name] laboratory and transported in batches to consortium partners for analyses in line with study SOP’s and MTA’s. Additional sections will be subjected to molecular analyses, including genomic, mRNA expression and protein studies by the RE-IMAGINE consortium academic and industry partners.

Both H&E slides and FFPE tissue blocks will be returned to the relevant NHS pathology department.

Instructions on postage and packing will be shared with sites at SIV.

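### The cross-sectional risk model admits biopsy-tissue predictors of an outcome read from the same biopsy, so any model that uses them cannot give a referred man's pre-biopsy risk

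*Protocol*

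**What the plan says.** Protocol Section 3 (Cross Sectional Component objective) aims at a baseline risk stratification system for referred men and defines its target: "By risk we mean the probability of harbouring clinically significant prostate cancer". It then lists the predictor sources: "These characteristics will be collected from clinical records, mpMRI images, blood, urine and biopsy tissue samples".

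Section 3.1.1 defines the outcome: "Presence of clinically significant prostate cancer confirmed on biopsy, defined as any Gleason pattern 7 or greater".

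The longitudinal objective repeats the predictor sentence, but its target differs: "By risk we mean the probability of developing cancer, cancer progression, metastasis and death".

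Tissue comes from two places.

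- **Research cores** (Section 5.1, Visit 1): "Up to three additional biopsy cores will be taken at the time of the standard of care biopsy". Two are aimed at the MRI lesion and one is a control from the other side.
- **Diagnostic material** (Section 5.1, Non-Visit, and Section 13.4): blocks and slides of the standard biopsy are requested once that biopsy has been reported. Section 13.4 allows for "morphological features captured using computer-based algorithm to identify H&E based biomarkers for improved patient risk stratification", as something that could be done.

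Section 9 plans stepwise logistic regression for the cross-sectional outcome, followed by a Bayesian pipeline: "This will be done both for the full covariate set and for the individual covariate streams (e.g. imaging, genomic, phenotypic"). The purpose is to compare how well the different sources predict.

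**The concern.** One predictor sentence serves two components and suits only one. In the longitudinal component the outcome comes later, so tissue is a proper baseline predictor. In the cross-sectional component the tissue comes from the procedure that determines the outcome.

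Two problems follow for any cross-sectional model that includes tissue.

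1. **Timing.** The predictor does not exist when a referred man needs his risk estimated. Once it exists, the biopsy has answered the question.
2. **Overlap with the outcome.** Gleason grade is read from the appearance of the stained slides. Features computed from those slides may partly restate the outcome.

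At stake are the full-covariate model and the comparison of sources. Tissue could gain an advantage there that no pre-biopsy marker can match, and stepwise selection could drop useful blood, urine or imaging markers in its favour. Section 9 also carries the source-specific risk signatures into the second-stage latent class analysis, so the effect would pass on to the proposed patient subgroups.

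**Working it through.** **Order of events, from the protocol.**

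- MRI: before entry, as an inclusion criterion (Section 7.1).
- Blood and urine: always before biopsy (footnote to Table 1).
- Research cores: same session as the diagnostic biopsy (Section 5.1, Visit 1).
- Blocks and slides: in Table 1 their collection shares the 3 to 6 week column with the biopsy results.

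A clean pre-biopsy predictor set therefore exists, and tissue lies outside it. Nothing in the protocol bars tissue from the cross-sectional models in Section 9.

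**The plan's own figures (Section 9).** 1,777 × 0.75 = 1,332.75 (stated 1,333); 1,333 × 0.75 = 999.75 (stated 1,000); 1,000 × 0.60 = 600 cancers; 600 × 0.66 = 396 clinically significant; 1,000 − 396 = 604 not. These reproduce. Among the 604 non-cases, 600 − 396 = 204 have insignificant cancer and 400 have no cancer.

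**A tissue marker that only detects tumour.** The protocol gives no marker accuracy. Assume sensitivity of 0.85 to 0.95 and specificity of 0.90 to 0.95 for any tumour, with Gleason 6 tumour detected as readily as higher grade. For a binary marker, AUC = (sensitivity + specificity)/2. Against any tumour this gives (0.85 + 0.90)/2 = 0.875 up to (0.95 + 0.95)/2 = 0.95. The study outcome is Gleason 7 or greater, however, so the 204 insignificant cancers count as false positives when detected:

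- Sensitivity 0.85, specificity 0.90: false-positive rate (204 × 0.85 + 400 × 0.10)/604 = 213.4/604 = 0.353; AUC = (0.85 + 0.647)/2 = 0.75.
- Both 0.95: (204 × 0.95 + 400 × 0.05)/604 = 213.8/604 = 0.354; AUC = (0.95 + 0.646)/2 = 0.80.
- Perfect tumour detection: 204/604 = 0.338; AUC = (1 + 0.662)/2 = 0.83.

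An AUC above 0.83 therefore needs a marker that also tracks grade.

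**Effect of adding tissue to a pre-biopsy score.** Assume both scores are normal with equal variance in cases and non-cases, and independent given the outcome. With z = Φ⁻¹(AUC), the combined AUC is Φ(√(z₁² + z₂²)). Example: AUCs of 0.75 and 0.85 give z of 0.674 and 1.036; √(0.455 + 1.074) = 1.237; Φ(1.237) = 0.89. A simulation at 39.6% prevalence agrees. The pre-biopsy AUC is assumed to be 0.70, 0.75 or 0.80.

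| Tissue marker AUC | Pre-biopsy 0.70 | Pre-biopsy 0.75 | Pre-biopsy 0.80 |
| --- | --- | --- | --- |
| 0.75 | 0.80 | 0.83 | 0.86 |
| 0.85 | 0.88 | 0.89 | 0.91 |
| 0.95 | 0.96 | 0.96 | 0.97 |
| 0.99 | 0.99 | 0.99 | 0.99 |

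The last row is close to reading the grade itself. None of the gain in any row is available to a man who has not yet had his biopsy.

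**The case against.** The strongest reply is that the protocol fixes less than the concern supposes. Section 3 speaks of exploring risk. Section 9 leaves the factor list to plans agreed before outcome data are inspected, and it also models the streams separately, so tissue-free results are planned or possible. The genomic stream is not tissue alone: Section 5.1 (Analyses) plans genomic work on blood and urine as well, and Section 2 describes plasma DNA. The frozen research cores are additional to the diagnostic tissue (Section 13.3), so molecular assays on them are not part of the grading. Their association with grade is a fair exploratory question, and the Introduction names precise diagnosis and biomarker re-calibration as purposes. Section 13.4 makes the slide features conditional and does not assign them to the cross-sectional model.

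Much of this stands, and it rules out several stronger readings.

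- A reader might infer that the whole cross-sectional analysis is circular. Only models containing tissue are exposed, so it is also wrong to say that results on all 396 cases are compromised.
- A reader might expect tissue to reach 0.875 to 0.95 simply by detecting tumour. That range is for any tumour, not for this outcome.
- A reader might think the Section 2 hypothesis, that tumour complexity and heterogeneity "integrated with imaging will improve risk stratification over and above the current best predictor" (histological grade), is defeated because grade is the cross-sectional outcome. Its context is prognosis, and the longitudinal component can test it.

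The reply does not remove the core point. Section 3 itself names tissue as a predictor source for this target, so an analysis plan faithful to it would include tissue.

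**Conclusion.** The concern holds for tissue-containing cross-sectional models and for any source comparison that includes tissue. Such models do not estimate the quantity the objective defines for referred men. The timing problem applies to all tissue. The overlap problem applies most directly to features of the graded blocks and slides, and much less to molecular assays on the separate research cores.

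The size of the inflation cannot be derived from the protocol, which gives no AUC or marker accuracy. Under the stated assumptions, a tumour-only marker reaches about 0.75 to 0.80, with a ceiling of 0.83. With an assumed pre-biopsy AUC of 0.75, adding a tissue marker of AUC 0.75 to 0.95 lifts the total to between 0.83 and 0.96. These figures rest on equal detection of Gleason 6 tumour and on conditional independence, respectively. They illustrate the mechanism and do not forecast results. The conclusion on timing needs none of them.

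**What to change.** In Section 3 (Cross Sectional Component objective) and Section 9 (Statistical Analysis):

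- State that the cross-sectional risk model and its comparison of information sources use only predictors available before biopsy: clinical records, mpMRI, blood and urine.
- Report associations between tissue features and concurrent grade separately, as exploratory characterisation, and exclude histological features that define the outcome.
- Keep tissue as a baseline predictor in the longitudinal models, where the existing wording already fits.

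This is a change of wording. No data collection, sample-size figure or assay changes. The downside is that tissue assays, including those of consortium partners, no longer contribute to the headline cross-sectional discrimination.
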